#### 2.12.2 Per-protocol set

The per-protocol set (PPS) will include all subjects who complete protocol-specified treatments without serious protocol violations. The exact definition of a serious protocol violation will be finalized at the time of data review, which may generally include (but will not be limited to) the following situations: failure to meet the main inclusion criteria, other treatment that seriously interferes with efficacy evaluation after inclusion, poor compliance, and follow up after the time window for follow-up has closed. PPS is a secondary analysis set for validity, but if the results of the FAS and PPS are inconsistent, sensitivity analyses and subgroup analyses will be conducted, and possible causes of the inconsistencies will be investigated.

#### 2.12.3 Safety set

In this trial, the safety analysis will be performed using the safety analysis set (SS). The SS will include those who receive at least one LSZ capsule treatment and one safety evaluation during the study period.

#### 2.12.4 Analysis of the primary outcome

The primary outcome, the proportion of patients with favorable outcome in each group, will be compared by the chi-square test. Assessment of the primary effect will involve the analysis of differences in mRS scores between the LSZ treatment and placebo groups using ordinal logistic regression; the results will be expressed as odds ratios (ORs) with 95% confidence intervals (CIs). Both covariate-adjusted analysis and covariate-unadjusted analysis will be performed. Adjusted analyses will incorporate the following covariates: age, sex, baseline National Institutes of Health Stroke Scale (NIHSS) score, TOAST classification. Adjusting for prognostic factors enhances statistical power in clinical trials, which can also correct for imbalances in baseline prognostic variables, reducing data variability (Optimising the Analysis of Stroke Trials (OAST) Collaboration et al., 2009; Kahan et al., 2014).

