## 2 Methods and design

### 2.1 Study design and patient selection

The LONGAN trial is a prospective, multicenter, randomized, placebo-controlled, double-blind, parallel-group, superiority trial that enrolls patients from stroke and rehabilitation units in China. This study will be conducted at 15 sites across China. The primary objective of the trial is to test the hypothesis that LSZ capsule is superior to the placebo for increasing the proportion of favorable functional status, defined as a modified Rankin Scale (mRS) score ≤1 at 90 days. The secondary objective is the assessment of any other benefits or harms from the end of the treatment period up to 180 days after the stroke. Participants will be followed up at 30, 90 and 180 days after randomization (D30, D90 and D180, respectively) to collect efficacy and safety outcomes in person. Patient enrollment will begin in May 2022 and end in June 2023. Figure 1 presents a schematic diagram of the patient timeline. The trial was approved by the institutional review board of Dongzhimen Hospital, Beijing University of Chinese Medicine, Beijing, China and registered in public clinical trial database (No. 2021DZMEC-198-02; ClinicalTrials.gov Identifier NCT 05277311). We described this study protocol according to the SPIRIT 2013 Statement, and the complete checklist is available.

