### 2.2 Randomization, allocation, and blinding

Eligible patients who consent to participate will be assigned to the LSZ capsule experimental or control group at a 1:1 ratio using permuted block randomization stratified according to medical centers. The randomization program will be generated by an independent statistician using SAS software v9.4 (SAS Institute, Inc.; Cary, NC, United States) and stored in sealed, sequential, opaque envelopes. The site pharmacist will retain these envelopes, which will be assigned in the order specified by the statistician.

At randomization, study medications will be packaged into a large box containing LSZ capsules or LSZ placebo capsules. When the patient is discharged, the trial medication will be continued and documented on the discharge summary and on the patient’s list of ongoing medications. At 30 days after randomization, patients will be instructed to bring partial empty boxes to this follow-up. Patients who stop taking the allocated treatment early will be followed up, and their data will be included in the primary analyses. The reason for stopping the treatment prematurely, e.g., a SAE, will be recorded in the patient’s electronic case report form (CRF).

Active and placebo capsules with identical appearances, colors, and flavors will be prepared by Buchang Pharmaceutical Co, Ltd. The placebo capsules are visually identical to the LSZ capsules, even when broken open. In the study, each patient’s medications will be prepared as a unit-dose kit according to the predetermined randomization schedule. The site pharmacies will not disclose the randomization assignments unless information is required for patient treatment in exceptional circumstances. The clinical center pharmacist will be unblinded to the treatment, but all investigators, participants, caregivers, and data analysts will be blinded to treatment assignments throughout the trial until the blind codes are revealed. Investigators can request emergency unblinding in cases of serious adverse events (SAEs) suspected to be associated with the investigational medicine.

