### 2.4 Efficacy outcomes

The primary outcome will be the proportion of patients with a favorable outcome, which is defined as mRS ≤1 on D90 (Rankin, 1957). The mRS is an ordinal scale ranging from 0 to 6 (Lees et al., 2012), with 0–1 indicating no disability, 2 to 5 indicating disability (increasing from 2 to 5), and 6 indicating death. The secondary outcomes will be as follows: 1) distribution of mRS scores [will be measured on D30 and D90]; 2) proportion of patients with good functional status [defined as mRS score ≤2; will be measured on D30 and D90]; 3) neurological deficit improvement [defined as a change in the National Institute of Health Stroke Scale (NIHSS) score (Brott et al., 1989), ranging from 0 to 42, with higher scores indicating more severe strokes; will be measured at baseline, D30, and D90]; 4) proportion of poor health-related quality of life (poor-HRQOL) [available EuroQol-5D Questionnaire (EQ-5D) data will be used to calculate EQ-5D index scores (Dorman et al., 1997). Poor-HRQOL is defined as an EQ-5D index score ≤0.5 and will be measured on D30 and D90. The EQ-5D index score is measured on a scale between 0 (death) and 1 (full health). The patient’s mobility, self-care ability, daily activities, feelings of pain or discomfort, and feelings of anxiety or depression contribute to EQ-5D. Here, each aspect will be divided into three levels (Rabin and de Charro, 2001): no problems, moderate problems, or extreme problems. The EQ-5D index score (preference-based health status) will be determined using the population-based preference weight values for five dimensions of the scale (Dolan, 1997; Shaw et al., 2005; Liu et al., 2014). This study will use preference weights applicable to the Chinese population (Liu et al., 2014)]; 5) proportion of patients with functional independence [defined as Barthel Index (BI) ≥90 (Mahoney and Barthel, 1965); BI is a conventional scale used to assess the activities of the daily living of stroke patients involving 10 items with a maximum score of 100 points; will be measured on D30 and D90]; 6) changes in motor function [measured by the Fugl–Meyer Motor Scale (FMMS) score (Fugl-Meyer et al., 1975), ranging from 0 to 100, with lower scores indicating poorer motor status; the change from baseline of the FMMS will be measured on D90]; and 7) changes in cognitive function [measured by the Montreal Cognitive Assessment (MoCA) score (Nasreddine et al., 2005), ranging from 0 to 30, with less than 26 indicating cognitive impairment; the change in MoCA from baseline will be measured on D90].

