#### 2.12.5 Analysis of the secondary and exploratory outcomes

For dichotomous outcomes, including the proportion of patients of good functional status (mRS ≤2), the proportion of poor-HRQOL (EQ-5D index score ≤0.5), the proportion of patients with functional independence (BI ≥ 90), the distribution of mRS scores, recurrence rates of stroke, and the proportion of new combined vascular events, a comparison of how patients with these outcomes are distributed among the two groups will be assessed using a chi-square test or Fisher’s exact test and presented as OR estimates and 95% CIs using logistic regression. Moreover, the distribution of functional outcomes on the mRS in both groups will be expressed in histograms. For other secondary outcomes of continuous variable, the changes from baseline to the endpoint of treatment for the above outcomes, including neurological deficit, motor function and cognitive function will be analyzed using the Student’s t test or Wilcoxon rank-sum test where appropriate. For survival data, the Kaplan-Meier method will be used to estimate the survival rate of each group; a survival curve will be drawn, and the log-rank test will be used to evaluate the curative effect. Cox proportional hazards models will be used to calculate hazard ratios (HR) and 95% CIs between the two treatment regimens. The central effect will be set as a random effect in all models. All statistics will be evaluated using two-sided tests, and *p* < 0.05 will be considered statistically significant.

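### Section 2.12.4 gives a primary role to two different analyses of the mRS, a chi-square test of mRS ≤1 and an ordinal regression of the whole scale, and does not say which decides

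*Protocol article*

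**What the plan says.** Section 2.1 states the hypothesis that "LSZ capsule is superior to the placebo for increasing the proportion of favorable functional status". Section 2.4 defines the endpoint: "The primary outcome will be the proportion of patients with a favorable outcome, which is defined as mRS ≤1 on D90". Section 2.11 sizes the trial on 60% versus 69% for that proportion.

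Section 2.12.4, on the primary outcome, makes three statements in a row:

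- On the proportion: "the proportion of patients with favorable outcome in each group, will be compared by the chi-square test".
- On the effect: "Assessment of the primary effect will involve the analysis of differences in mRS scores", by ordinal logistic regression, reported as odds ratios with 95% confidence intervals.
- On adjustment: "Both covariate-adjusted analysis and covariate-unadjusted analysis will be performed". The covariates are age, sex, baseline NIHSS and TOAST class.

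The whole mRS distribution at days 30 and 90 is the first secondary outcome in section 2.4. Section 2.12.5 places it in the list that opens "For dichotomous outcomes, including the proportion of patients of good functional status", to be analysed by chi-square or Fisher's exact test and logistic regression. The same section sets two-sided p < 0.05 for all tests and makes centre a random effect in all models. No section ranks the analyses, orders the tests or divides alpha between them.

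**The concern.** The word primary is attached to two analyses that estimate different things. The chi-square test addresses a difference in the proportion with mRS ≤1. The ordinal model gives a common odds ratio over all seven levels, so it also responds to movement between 0 and 1 or between 3 and 4, which the primary outcome ignores. The only effect estimate promised under the primary-outcome heading belongs to the ordinal model, so the headline odds ratio would not describe the stated endpoint.

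If the two disagree, the plan does not say which one settles whether the trial succeeded. The adjusted and unadjusted versions leave a further choice open. The abstract and introduction say the plan is published to prevent selective analysis and reporting, and on the primary endpoint this text leaves room for it.

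**Working it through.** **1. Which analysis does the sample size belong to?** Inputs from section 2.11: 60% versus 69%, two-sided 5%, power 90%, 1:1 allocation, 10% loss.

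Two proportions, pooled variance, mean proportion 0.645:

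n = [1.960 × √(2 × 0.645 × 0.355) + 1.282 × √(0.60 × 0.40 + 0.69 × 0.31)]² / 0.09² = 592 per arm, 1,184 in total.

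With continuity correction:

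n = (592/4) × [1 + √(1 + 4/(592 × 0.09))]² = 614 per arm, 1,228 in total.

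The plan states 1,238, within 1% of the corrected figure, and 1,238 / 0.90 = 1,376 as stated. The trial is therefore sized for a test of two proportions. At 619 per arm the uncorrected test has power Φ[(0.09 × √619 − 1.960 × 0.6767) / 0.6737] = 91.2%.

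**2. How far apart are the two analyses?** The documents give only P(mRS ≤1), so the rest of the scale must be assumed. Three distributions over mRS 0 to 6, each with 60% at 0–1, were used:

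- A: 25, 35, 15, 10, 8, 4, 3%
- B: 15, 45, 12, 12, 8, 3, 5%
- C: 35, 25, 14, 10, 8, 4, 4%

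Each scenario had 619 per arm and 40,000 simulated trials. A rank test (the proportional-odds score test) stood in for the unadjusted ordinal regression. Rejection rates at two-sided 5%:

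| Scenario | Chi-square | Ordinal | Either | Disagree |
|---|---|---|---|---|
| No effect | 5.0–5.1% | 4.9–5.0% | 7.1% | 4.1–4.4% |
| Proportional odds, OR (0.69/0.31)/(0.60/0.40) = 1.48 | 91% | 97% | 97% | 6.3–6.8% |
| 9 points move from mRS 2 to 1 only | 91% | 20–39% | 91% | 52–72% |
| 9 points move from mRS 1 to 0 only | 5% | 39–40% | 42–43% | 39–40% |

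The last two rows are deliberate extremes. They show that the two tests answer different questions; they are not forecasts.

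**3. Adding the adjusted ordinal test.** This used a latent-normal mRS, one covariate correlated with the latent outcome, and rank-based linear models in place of the ordinal regressions. With no effect, at least one of the three tests (chi-square, ordinal unadjusted, ordinal adjusted) was significant in about 8% of trials at correlation 0.3 and 9.1–9.5% at 0.5. These rates count both directions. False claims of benefit are roughly half: 7.1 / 2 ≈ 3.6% for two tests and 8.0 / 2 = 4.0% to 9.5 / 2 ≈ 4.8% for three, against a nominal 2.5%. At 60% versus 69% under this model, the chi-square and unadjusted ordinal tests again disagreed in about 7% of trials.

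**4. Power of the binary options.** On the same model, power for mRS ≤1 is about 91% unadjusted and 92–95% covariate-adjusted, at correlations of 0.3 to 0.5.

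**The case against.** The best defence is that the order of the text settles the matter. The chi-square test comes first, its subject is the primary outcome, and it matches the objective, the endpoint and the sample size, so the ordinal model can be read as supportive. That is a natural reading, and one sentence would make it explicit. But the text does not say so, and it attaches the words primary effect to the ordinal model. Nor can the matter be left to an unseen analysis plan: the introduction says the article summarises that plan for the primary analysis, and the problem is two stated analyses, not a missing detail.

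Three stronger readings are tempting and are not supported:

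- A reader might count three primary p-values. Section 2.12.4 uses the primary label twice. The sentence on adjustment carries no such label, and for the regression the section promises odds ratios and intervals, although section 2.12.5 applies p < 0.05 generally.
- A reader might conclude that the methods for the primary outcome and secondary outcome 1 were accidentally swapped. The layout suggests it, but that is an inference about drafting. A chi-square test is also valid on a 2 × 7 table, though it ignores the ordering.
- A reader might fault the chi-square test for ignoring centre, given "permuted block randomization stratified according to medical centers", and the covariates. An unadjusted test is a legitimate primary analysis. Ignoring a stratification factor generally makes it conservative, and it already exceeds the planned 90% power. Adjustment is an improvement here, not the correction of an error.

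The error rates also assume that any significant result would be picked after the fact. They describe what the wording permits, not what the trial team would do.

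**Conclusion.** The point holds. Section 2.12.4 gives two different estimands a primary role, leaves adjusted and unadjusted versions unranked, and names no deciding analysis. The conflict is visible in the text and needs no simulation. Its size does rest on assumptions: a two-sided type I error of about 7% if either the chi-square or the unadjusted ordinal test may decide, and 8% to 9.5% as a worst case with the adjusted ordinal test added. The 7% figure barely changes across the three assumed mRS distributions; the higher range also depends on the assumed covariate correlation.

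As a separate and smaller fault, section 2.12.5 lists a seven-level ordinal outcome as dichotomous. Because the main conflict bears on the trial's confirmatory conclusion, it should be resolved before unblinding.

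**What to change.** Name one analysis of day-90 mRS ≤1 whose p-value decides. Either option removes the conflict:

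- the chi-square test, reported with a risk difference or binary odds ratio and 95% confidence interval; or
- a binary logistic regression on treatment, age, sex, baseline NIHSS and TOAST class, with centre as a random effect, reported with its odds ratio and 95% confidence interval.

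The second is preferable: the covariates are already collected, it agrees with the rule on centre in section 2.12.5, and it adds a little power. Its small downside is reliance on a model. Whichever is chosen, make the other binary analysis a sensitivity analysis.

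Move the ordinal logistic regression to secondary outcome 1, and take the distribution of mRS scores out of the dichotomous list in section 2.12.5. The cost is wording only, with no new data and no change to 1,238 or 1,376.

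### The primary outcome is the proportion with mRS ≤1 at D90, but section 2.12.4 measures the primary effect with an ordinal model of the whole mRS, a different estimand, and does not say which result decides the trial

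*Protocol article*

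**What the plan says.** Section 2.1 sets the hypothesis as "LSZ capsule is superior to the placebo for increasing the proportion of favorable functional status", meaning mRS ≤1 at 90 days. Section 2.4 agrees: "The primary outcome will be the proportion of patients with a favorable outcome, which is defined as mRS ≤1 on D90". Section 2.11 sizes the trial on that proportion, 60% in the control arm and 69% in the experimental arm.

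Section 2.12.4 then has three statements in sequence:

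- On the test: "The primary outcome, the proportion of patients with favorable outcome in each group, will be compared by the chi-square test".
- On the effect measure: "Assessment of the primary effect will involve the analysis of differences in mRS scores between the LSZ treatment and placebo groups using ordinal logistic regression", with the result given as odds ratios and 95% confidence intervals.
- On adjustment: "Both covariate-adjusted analysis and covariate-unadjusted analysis will be performed", the covariates being "age, sex, baseline National Institutes of Health Stroke Scale (NIHSS) score, TOAST classification".

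The full scale also appears in section 2.4, where it opens the list of secondary outcomes: "1) distribution of mRS scores [will be measured on D30 and D90". Section 2.12.5 places that distribution among the dichotomous outcomes, to be analysed by chi-square or Fisher's exact test with logistic regression. The same section applies a two-sided 0.05 threshold to every test and gives no ranking.

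**The concern.** The label of primary effect is attached to a quantity other than the primary outcome. A common odds ratio over mRS 0–6 pools shifts at every cut of the scale. It moves when patients go from 1 to 0 or from 5 to 3, neither of which changes the proportion with mRS ≤1. The models are also crossed over: the binary primary outcome gets the ordinal model, and the ordinal secondary outcome gets a binary-type analysis.

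The main consequence concerns the estimate. Followed as written, the plan gives its only named primary odds ratio and interval for a question that the trial was not sized to answer, while the planned 9-point difference has no named effect measure with an interval.

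A second consequence is conditional. Three results stand in the primary section: chi-square, unadjusted ordinal and adjusted ordinal. If the plan is read as leaving them unranked, more than one test has a chance to support the claim at the 5% level.

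**Working it through.** **1. The design rests on the binary comparison.** Inputs from section 2.11: p₀ = 0.60, p₁ = 0.69, two-sided α = 0.05, power 90%, 1:1 allocation.

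- Mean proportion: p̄ = (0.60 + 0.69)/2 = 0.645.
- Per arm without continuity correction: n = [1.960·√(2·0.645·0.355) + 1.282·√(0.60·0.40 + 0.69·0.31)]² / 0.09² = (1.326 + 0.863)² / 0.0081 ≈ 592, total 1,184.
- With continuity correction: n′ = (n/4)·[1 + √(1 + 4/(n·0.09))]² ≈ 614, total 1,228. The plan states 1,238, which is within 1%.
- Allowance for 10% loss: 1,238/0.90 = 1,375.6, rounded up to 1,376, as stated.

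So 1,238 is the size of a two-proportion test. (Section 2.11 also mentions a 5% superiority margin. The stated total fits only a test against zero difference, and that is the test used here.)

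**2. The planned effect on the binary scale.** Risk difference 0.69 − 0.60 = 0.09. Risk ratio 0.69/0.60 = 1.15. Odds ratio (0.69/0.31)/(0.60/0.40) = 1.48.

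**3. No true effect: how often does something reject?** The documents give no full mRS distribution, so two were assumed for scores 0 to 6, each with 60% at mRS ≤1: A = 25/35/12/10/10/4/4% and B = 25/35/14/12/8/3/3%. The adjusted model carried prognostic covariate information of assumed strength.

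| Rule for claiming success | Two-sided rejection under the null |
|---|---|
| Chi-square alone | about 5% |
| Chi-square or unadjusted ordinal | about 7.4% (7.2–7.7% across runs of 10,000 or more and three assumed distributions) |
| Any of the three | roughly 9–10% (8.6–10.5% depending on covariate strength) |

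Three independent tests would give 1 − 0.95³ = 14.3%, so the correlation between the tests removes part of the inflation. These figures count rejections in both directions. For a false claim of benefit, either of two tests gives about 3.8% against a nominal 2.5%.

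**4. True effect: do the binary and unadjusted ordinal tests agree?**

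| Scenario | Per arm | Binary significant | Ordinal significant | Disagree |
|---|---|---|---|---|
| Proportional shift, OR 1.48 (60% to 69%) | 619 | about 91% | 96–97% | about 7% |
| 60% to 69%, only by moving mRS 2 to 1 (A) | 688 | 94% | about 30% | up to about 65% |
| Same shift (B) | 619 | 90% | 29% | 62% |
| 9 points from mRS 1 to 0, mRS ≤1 unchanged (A) | 619 | about 5% | 40% | about 40% |

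In the third row the median common odds ratio was 1.15 while the binary odds ratio was 1.48. The ordinal estimate can therefore differ greatly from the effect on the primary outcome even when the planned binary gain is fully present.

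**The case against.** The strongest defence is that a deciding test can be read from the text. Section 2.12.4 opens with chi-square for the primary outcome, and every other section that defines the primary question is binary. On that reading the ordinal odds ratio is an additional measure and the type I error is 5%. This largely stands. A reader might infer that three tests compete for one claim and that the 5% level is therefore lost. The article does not say that any of the three may carry the claim, so the inflation holds only on an unranked reading.

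A reader might also infer that the primary outcome will get no estimate at all. That goes too far. The proportion in each arm will be reported, so the difference will be visible, and the sentence on adjusted and unadjusted analyses could cover a binary model. What can be said is that no binary effect measure with a confidence interval is named.

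The large disagreement figures come from shifts built to separate the two tests. In the ordinary proportional case the disagreement is small and the ordinal test is the more powerful.

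The defence does not remove the mismatch. Even if chi-square decides, the primary effect is still defined on another estimand, one that section 2.4 lists as secondary and section 2.12.5 misclassifies as dichotomous. An unseen analysis plan is a weak answer, because the introduction says that the article summarises that plan for the primary analysis. The text here is inconsistent, not merely brief.

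**Conclusion.** Section 2.12.4 is wrong as written. It ties the primary effect to the full mRS although the objective, outcome and sample size rest on mRS ≤1 at D90, and it does not say that chi-square alone decides. This part follows from the text and needs no simulation.

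The numerical cost depends on how the plan is read and on the assumed mRS distributions and covariate strength. Type I error is 5% if chi-square alone decides, about 7.4% if the unadjusted ordinal test could also carry the claim, and roughly 9–10% for any of the three. Disagreement between the binary and ordinal results is about 7% under a proportional odds ratio of 1.48 with 619 per arm, and up to about 65% when the whole gain comes from mRS 2 moving to 1. The documents do not support calling the inflation certain or the 65% typical.

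**What to change.** In section 2.12.4:

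- State that one named test of the proportion with mRS ≤1 at D90 decides the trial.
- Report the effect on that binary outcome with a 95% confidence interval. Either the risk difference or the binary odds ratio will do; the choice is the sponsor's.
- Assign the ordinal model to the first secondary outcome, and label the other adjusted or unadjusted variants as supportive.

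In section 2.12.5, take the mRS distribution out of the list of dichotomous outcomes.

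The cost is a few sentences, settled before unblinding. The sample size stays as it is: 619 per arm gives about 91% power for 60% versus 69%, or about 90% with continuity correction. The small downside is that the ordinal odds ratio is no longer a headline result, and its higher power under a proportional shift is not used for the primary claim.
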